## INCLUSION

Decisions on inclusion are taken by a licensed psychologist and the principal investigator ([name]) together.

## BASELINE ASSESSMENT

Before the start of treatment, participants will conduct baseline assessments consisting of CATS-2, MFQ, WSAS, KIDSCREEN and TIC-P.

## DURING TREATMENT

Weekly during the treatment period, CATS-2, a question about suicidal thoughts and questions about adverse events are administered.

## POST ASSESSMENT

Post-assessment is done using the same outcome measure as for the baseline assessment but with the addition of a self-rating questionnaire about acceptability and satisfaction with the treatment, Client Satisfaction Questionnaire (CSQ-8). Interviews with the participants and their caregivers will be conducted after completion of treatment.

## 1-MONTH FOLLOW UP

The same self-rated assessment questionnaires as at baseline will be used with the addition of the CAPS-5-CA interview. Qualitative interviews will also be conducted and scheduled separately. The assessment will include the need for further psychiatric care.

## 6-MONTH FOLLOW-UP

Long-term follow-up assessments will be conducted at 6 months after completed treatment using the CAPS-5-CA and the same self-rated assessment questionnaires as baseline.

## ADVERSE EVENTS

Adverse events data will be collected every week during the treatment period and at each assessment point using a self-rating questionnaire with a free text option where participant is instructed to describe the possible event in detail. If the participant reported any adverse event, additional follow-up questions about intensity, duration etc. will also be given and assessed by the research team and designated therapist. Eventual adverse events will be handled in accordance with good clinical practice.

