## OUTLINE

### INCLUSION CRITERIA

#### Inclusion criteria

- 13-17 years,
- Primary PTSD diagnosis
- Fluent in Swedish
- Access to the Internet at home or can use vouchers for internet-access to their phone.
- Parent/guardian willing and able to take part in treatment.

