## SAMPLE SIZE

## OUTCOME MEASURES

The power analysis for the RCT is based on the gold-standard interview CAPS-5 where a clinically significant difference in treatment effects is 10 points, which is the between groups difference we aim to detect. With a standard deviation of the CAPS-5 to be 20, this represents a standardized mean difference in terms of Cohens  $d$  of 0.5 and to use it conservatively we used Cohens  $d$  0.4 in our calculations. The estimated number needed is then  $N=240$  (moderate between-group effect size against active control condition at 1-month post-treatment; 95% power, 10% data attrition rate, and an  $\alpha$  level of 0.04). All analysis will be conducted according to the intent to treat principle and we will follow the CONSORT guidelines in reporting and analyzing the data.

The primary hypothesis (clinician-rated CAPS-5-CA) will be evaluated using a linear mixed-effects model with fixed effects of time and group, their interaction, as well as random intercept and slope. Treatment response will be defined as at least 6 points improvement on the CAPS-5 between baseline and participants' last available measurement between baseline and 12-month follow-up (adapted from Schnurr & Lunney, 2016). Secondary self-rated outcomes will be estimated using linear mixed-effects models with repeated measurements and fixed effects of time and group, their interaction, as well as a random intercept and slope.

We will follow the Consolidated Health Economic Evaluation Reporting Standards (CHEERS) guidelines to report the health economic evaluation and look at both direct costs (e.g., therapist time per patient) and other societal costs (e.g., absence from school, caregivers' absence from work). Cost differences between iTF-CBT and the active control condition will be calculated, as well as the incremental cost-effectiveness ratio (ICER). The ICER is a global estimate of cost-effectiveness and represents the additional cost that is associated with the additional clinical effect in one intervention compared with another. Intra-Class Correlations will be used to calculate Interrater agreement on the CAPS-5-CA.

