## OUTCOME MEASURES

- Clinician Administered PTSD Scale Children and Adolescent version 5 (CAPS-5-CA), the gold standard clinical interview to assess PTSD symptom severity and diagnosis of PTSD [42] at baseline and the 1-month, 6-months and 12-months follow up.
- The Child and Adolescent Trauma Screen (CATS-2) at baseline, weekly through the treatment period, post-treatment and at the 1-month, 6-month and 12-month follow up.
- Mood and Feelings Questionnaire (MFQ) at baseline, post-treatment and at the 1-month, 6-month and 12-month follow up.

- The Education, Work and Social Adjustment Scale, Youth and Parent (EWSAS) at baseline, post-treatment and at the 1-month, 6-month and 12-month follow up.
- Treatment Inventory of Costs in Psychiatric Patients (TIC-P) at baseline, post-treatment and at the 1-month, 6-month and 12-month follow up.
- The Negative Effects Questionnaire (NEQ) at post-treatment and at the 1-month, 6-month and 12-month follow up.
- Assessment of Quality of Life KIDSCREEN at baseline, post-treatment and at the 1-month, 6-month and 12-month follow up.
- The Client Satisfaction Questionnaire (CSQ-8) at post-treatment.
- The Working Alliance Inventory (WAI) after completion of treatment module 3.
- The Credibility/Expectancy Questionnaire (CEQ) after completion of treatment module 1.

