## SAFETY PROCEDURES

Study participants will be able to report the occurrence of possible adverse events or undesirable treatment effects at any point through the study period either through the message function on the Internet platform or by contacting the study personnel by phone. A structured self-report questionnaire to capture the frequency and nature of possible adverse events will be used weekly through treatment and at all follow-up points. The participants

are asked to report and rate the short- and long-term discomfort of any adverse event on a scale from 0 ("did not affect me at all") to 3 ("affected me very negatively"). Reported incidents will be categorized depending on severity and frequency in line with GCP and will be crosschecked by KTA. All participants will be monitored by the study personnel throughout the study period to ensure participant safety. Written routines for situations of potential risk are made available to assessors and therapists. Serious adverse events (i.e. suicide attempts, serious violent incidents, or admission to hospital) will be documented and monitored by KTA. In case a participant's symptoms worsen during treatment, the therapist will carry out an immediate in-depth assessment of the symptoms and discuss this with the principal investigator for necessary actions.

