### ASSESSMENT OF ADVERSE EVENTS

AE is assessed in the treatment platform including an open question.

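### No guardian or record source is named for serious adverse events in an adolescent who stops responding, so such events may be missed

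*Protocol*

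**What the plan says.** The Adverse Events section collects harms weekly during treatment and at every assessment point, "using a self-rating questionnaire with a free text option where participant is instructed to describe the possible event in detail". What follows depends on that report: "If the participant reported any adverse event, additional follow-up questions about intensity, duration etc. will also be given".

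Safety Procedures describes the same kind of tool: "A structured self-report questionnaire to capture the frequency and nature of possible adverse events will be used weekly through treatment and at all follow-up points". It also lets participants report at any time by platform message or phone, says in general terms that study personnel monitor all participants, and provides for a therapist's assessment if symptoms worsen during treatment. For serious events it states: "Serious adverse events (i.e. suicide attempts, serious violent incidents, or admission to hospital) will be documented and monitored by KTA".

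Assessment of Adverse Events adds one line: "AE is assessed in the treatment platform including an open question". Definition of Serious Adverse Events includes death, life-threatening events, inpatient admission and lasting disability.

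Two possible further sources are already in the trial. The inclusion criteria require a "Parent/guardian willing and able to take part in treatment". The TIC-P is given at baseline, post-treatment and 1, 6 and 12 months. Neither is linked to the detection of adverse events.

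**The concern.** The events defined as serious are the ones most likely to stop an adolescent from answering. A death cannot be self-reported, and an admission or a suicide attempt can plausibly interrupt online answers. If detection depends mainly on the adolescent, it is weakest where completeness matters most.

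The results are affected as well as oversight. Adverse events are a listed secondary outcome and count towards acceptability (Primary Measures). The Implications section presents the trial's harms data as important to patients and providers, and argues for systematic collection on the ground that structured methods doubled the probability of an event being reported. For a participant who has stopped responding, the protocol specifies no structured method that still works.

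The dataset could also contradict itself. An admission entered in the TIC-P could be costed in the economic evaluation and yet be absent from the serious-event listing, because no comparison of the two is described.

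**Working it through.** The protocol states no figure on this point, so there is none to reproduce. The check sets each described route to an event beside the person who supplies the information.

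| Section | Route | Who supplies the information |
|---|---|---|
| Adverse Events | Self-rating questionnaire, weekly and at assessment points | Participant |
| Adverse Events | Follow-up questions on intensity and duration | Given if the participant has reported an event |
| Safety Procedures | Structured self-report questionnaire | Participant |
| Safety Procedures | Platform message or phone call | Participant |
| Safety Procedures | Therapist assessment on worsening | Therapist; how worsening is noticed in a silent participant is not stated |
| Safety Procedures | Monitoring by study personnel | Staff; no source, method or schedule given |
| Safety Procedures | External party documents and monitors serious events | How the event is discovered is not stated |
| Primary Measures | Weekly standardized checklist | Not stated |
| Assessment of Adverse Events | Open question in the treatment platform | Not stated |

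**Step 1. Named respondents.** Wherever an adverse-event tool has a named respondent, it is the adolescent. The remaining rows are staff activities without a described information source, or tools without a named respondent.

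**Step 2. A participant who has stopped responding.** The participant rows then yield nothing, and the follow-up questions are not triggered. The staff rows might still bring an event to light, but the text does not say how. No row names a guardian or a medical record.

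**Step 3. Sources already present.**
- The guardian takes part in treatment in every case (Inclusion Criteria, Intervention). The outcome list also names a parent version of the EWSAS at baseline, post-treatment and 1, 6 and 12 months, so a parent form is already foreseen at every point where the guardian questions would be asked.
- The TIC-P runs on the same schedule. The reference given for it describes a questionnaire on health-care use and lost productivity. Its respondent is not stated, and the follow-up sections call the baseline set self-rated. If the adolescent completes it, it is lost in the same silent participant.
- CAPS-5-CA interviews take place at 1, 6 and 12 months, with no question on serious events attached.

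**Step 4. Size.** The number of missed events would be (participants with no report over the relevant period) × (their serious-event risk) × (share not found by any other route). The protocol gives none of the three, so no figure is put on it.

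**The case against.** The strongest reply is that ascertainment does not rest on the platform alone. There is a phone route, each participant has a designated therapist, study personnel monitor everyone, and all participants are patients of the treating services. Live interviews follow at 1, 6 and 12 months, and the 1-month visit reviews the need for further care. This stands against any claim that events are found only through self-report in the platform, or that events in silent participants are certain to be missed. It does not answer the narrower point, because none of these is described as a way of finding serious events in someone who has stopped responding.

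Caregiver interviews are planned after treatment with a focus on acceptability, which includes treatment-related adverse events. So the guardian is not wholly outside the picture. These are qualitative interviews, however, and not a systematic question on admissions or other serious events at each assessment point.

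Three stronger readings are tempting and are not supported:

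- A reader might take the "10% data attrition rate" as the share giving no adverse-event report: 0.10 × 240 = 24 participants, or 0.10 × 140 = 14 with the sample size in the Objective section. That rate was set for the power calculation at 1 month. A participant missing then may already have given up to 12 weekly reports and a post-treatment report.
- A reader might infer that weekly collection stops when someone abandons treatment. The text ties it to the treatment period, which is 12 weeks, and does not say that it ends at drop-out. It does not say that it continues either.
- A reader might infer undercounting in the trauma-focused arm. That would need more distress-related non-response in that arm, which is possible but not shown.

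Reconciling cost data with safety data is often left to data-management documents. That is fair for the mechanics. The choice of who is asked about harms is fixed in this protocol.

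**Conclusion.** The point holds in a limited form. Every adverse-event tool with a named respondent depends on the adolescent, and no guardian or record source is named for a death, admission or suicide attempt in a participant who stops responding. Such events may therefore be missed. Staff monitoring is unspecified, not absent, and it may catch some or all of them.

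The size cannot be derived from the protocol, and the planned attrition rate is not a substitute. The conclusion rests on reading the monitoring statement as written, with no working procedure behind it that the protocol omits. If written routines already include a guardian query, stating so would settle the main part. This is more than missing detail, because the stated method can be improved cheaply with people and instruments already in the trial. It should be changed.

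**What to change.** Amend Adverse Events and Safety Procedures as follows. Each change can be made without the others.

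1. Ask the participating guardian a short set of adverse-event and hospital-admission questions at each assessment point, and whenever the adolescent's report is missing. This is the main remedy, because it does not depend on the adolescent answering.
2. Before analysis, check every hospital or emergency contact recorded in the TIC-P against the serious-event record, and state who completes the TIC-P. This is only a partial remedy: if the adolescent completes it and falls silent, it is missing too.
3. State that weekly adverse-event collection runs for the full 12 weeks whether or not the participant is still using the treatment. If that is already intended, this is a clarification only.

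The cost is a short guardian form and one reconciliation step, with no extra staff and no clinical procedure. The downside is a minor burden on guardians and possibly a higher reported event count, which the report should attribute in part to fuller ascertainment.

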## SAFETY PROCEDURES

Study participants will be able to report the occurrence of possible adverse events or undesirable treatment effects at any point through the study period either through the message function on the Internet platform or by contacting the study personnel by phone. A structured self-report questionnaire to capture the frequency and nature of possible adverse events will be used weekly through treatment and at all follow-up points. The participants

are asked to report and rate the short- and long-term discomfort of any adverse event on a scale from 0 ("did not affect me at all") to 3 ("affected me very negatively"). Reported incidents will be categorized depending on severity and frequency in line with GCP and will be crosschecked by KTA. All participants will be monitored by the study personnel throughout the study period to ensure participant safety. Written routines for situations of potential risk are made available to assessors and therapists. Serious adverse events (i.e. suicide attempts, serious violent incidents, or admission to hospital) will be documented and monitored by KTA. In case a participant's symptoms worsen during treatment, the therapist will carry out an immediate in-depth assessment of the symptoms and discuss this with the principal investigator for necessary actions.

## ETHICS

The study protocol and necessary documentation will be submitted to the Swedish Ethical Review Authority and must be approved for the study to commence.

## DATA MANAGEMENT

Case report form (CRF) data will be imputed to a data file. Statistical analysis will be performed by the research group and quality control and crosscheck will be performed by independent party. Data analysis will be done according to the intention to treat principle. The qualitative interviews will be analyzed using thematic analysis.

## TIME PLAN

Participants will be recruited and provided treatment starting winter 2023. Statistical analyses will be done immediately after the last participant has completed the post-

assessment. First publication is estimated to late 2024 or beginning of 2025. All data will be handled and eventually archived according to Swedish and European legislation.

2023 Q3-Q4: Develop the iTF-CBT treatment and set up the platform.

2024: Q1 Commencement of the RCT with an internal pilot study and follow-up assessments. Refinement of treatment.

2024 Q2-Q4: Completion of treatments and 6 months follow-up assessments. Analysis of results, manuscript draft of pilot part of RCT.

2026 Q4: Completion of 12 months follow-up assessments.

## PROCEEDINGS FOR ADVERSE EVENTS

### DEFINITION OF ADVERSE EVENTS

An Adverse Event (AE) is any untoward in a subject receiving an intervention which does not necessarily have a causal relationship with the intervention. An AE can be any unfavorable and unintended sign, symptom or disease temporally associated with receiving the intervention, whether or not related to it.

### DEFINITION OF SERIOUS ADVERSE EVENTS

Each AE is to be classified by the investigator as serious or non-serious. Seriousness is not defined by a medical term; it is a result or an outcome. An AE is defined as a Serious Adverse Event (SAE) if it:

- results in death
- is life-threatening
- requires inpatient hospitalization or prolongation of existing hospitalization
- results in persistent or significant disability/incapacity

### ASSESSMENT OF ADVERSE EVENTS

AE is assessed in the treatment platform including an open question.

### ASSESSMENT OF INTENSITY

Each AE is to be classified by the investigator as mild, moderate or severe.

**Mild:** Acceptable. The subject is aware of symptoms or signs, but they are easy tolerated.

**Moderate:** Disturbing. The AE is discomfort enough to interfere with usual daily activity.

**Severe:** Unacceptable. The subject is incapable to work or to do usual daily activities.

#### ASSESSMENT OF CAUSALITY

**Unlikely:** The event is most likely related to an aetiology other than the treatment.

**Possible:** A causal relationship is conceivable and cannot be dismissed.

**Probably:** Good reason and sufficient documentation to assume a causal relationship.

#### IMPLICATIONS

According to a recent study, only 21 % of the 132 reviewed articles on RCTs with psychological interventions reported adverse events (AE). Furthermore, Rief, Nestoriuc, von Lilienfeld-Toal, Dogan, Schreiber, Hofmann, Barsky and Avorn found that systematic assessment of AE led to a higher frequency of reported AE than less systematic ones, i.e. spontaneous reports. The probability for an AE to be reported was twice as high with structured assessment methods. Hence, the results from the collected AE data in this trial has the potential to provide important information for the scientific community as well as for patients and health care providers.

